### *Sample size*

Since the study is a pilot, 50 patients are intended to be recruited to participate in the randomized control trial. Sample size calculations will be made during the study, based on gathered data. If feasible, more than 50 patients may be enrolled in order to get sufficient statistical power.

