### *Randomization (sequence generation)*

Using statistical software, a statistician will generate a blocked randomization list that will be used to allocate patients to either the intervention or the control group. Blocks of four will be used.

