### *Decisional conflict (primary outcome)*

Decisional conflict will be assessed through a French version of OHRI Decisional Conflict Scale (18). The questionnaire will be filled at baseline and after a 2-month follow-up. Sixteen items evaluate 5 dimensions of decisional conflict (informed, values clarity, support, uncertainty, effective decision) using a Likert scale. Patients' responses range from 0 (strongly agree) to 4 (strongly disagree). Patients' responses are summed, divided by 16, and multiplied by 25. Consequently, the decisional conflict score ranges from 0 (low decisional conflict) to 100 (high decisional conflict). A score greater than 37.5 suggests that there is a meaningful decisional conflict, but a score that is less than 25 is not associated with it (33). The variable will nevertheless be analysed as a continuous one. The reliability of the OHRI Decisional Conflict Scale (English low literacy version) has been evaluated using a Cronbach's  $\alpha$ , which value was above the 0.7 threshold (34). Test-retest coefficient also supports its reliability (35). The scale has been shown responsive to change, because it is able to detect an effect size of 0.2 to 0.3 in studies that compare an intervention group to a control group (33).

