### *Data analysis*

Descriptive analyses will be performed in order to describe the study population: continuous variables will be described as means or medians, depending on normality of distributions, and categorical variables as proportions.

Generalised linear models will be used to compare the intervention and control groups on the dependent variables (41). For asthma knowledge, decisional conflict, compliance with maintenance/rescue/add-on pharmacotherapy, and asthma control, a normal distribution and an identity link will be used, since all 4 variables are expressed as continuous ones. Assumptions of normality, and homoscedasticity will also be checked. A log transformation could be used to correct departure from normality, if relevant. For compliance with pharmacotherapy, a binomial distribution and a log link will be used as this variable is expressed as a binary one. In models, effects for group (intervention and control), time (baseline and 2-month follow-up) and group-by-time interaction will be included. The effect of the shared decision making aids on health outcomes will then be estimated by the interaction term between the group and time. Mean differences (continuous variables) and prevalence ratios (dichotomous variable) have been

chosen as effect measures. In addition, generalized estimating equations will be used in order to take repeated measures into account.

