If covariates (asthma knowledge, age, body mass index, atopy, environmental triggers, and respiratory tract infections) are not distributed evenly between groups, we will adjust for them in analyses. Predictors of health outcomes will be incorporated into the model as confounders if they result in a >10% change in the effect measure, following a descending procedure. Exploratory subgroup analyses according to asthma severity will be conducted since pharmacotherapy and compliance with treatments are getting more complex with the severity of the disease. Statistical interaction of body mass index will also be exploratory assessed since this covariate is hypothesized to modify the effectiveness of intervention aiming at improving asthma control (42). In addition, exploratory statistical interaction of age, education and length of the patient's meeting with the asthma nurse will be evaluated since we hypothesize that the effect measure may vary according to the level of measurement of these variables. Regarding adherence to medication, sensitivity analyses will be carried out according to different cut-offs, that will range from 60 to 80% of inhaled prescribed doses.

SAS version 9.3 (SAS Institute Inc., Cary, USA) will be used to perform the statistical analyses, using PROC GENMOD. A 2-tailed *p*-value less than 0.05 will be considered indicative of statistical significance. Since the study is a pilot, power calculation will be made *a posteriori*. Alternatively, the study size is based on the number of patients that may realistically be recruited at the IUCPQ Research Center or Outpatient Asthma Clinic according to the timeframe. Nevertheless, sample size calculations will be made during the study, based on gathered data. If feasible, more patients may be enrolled in order to get sufficient statistical power.

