### **Bias**

Convenience sampling and loss to follow-up may induce selection bias in this pilot randomised controlled trial. In order to avoid loss to follow-up, visit 2 will be scheduled at the end of visit 1. In addition, we will phone enrolled patients in the week preceding visit 2 in order to ensure that they remember their appointment at the IUCPQ Research Center.

Self-reported questionnaires are at risk of nondifferential misclassification that may weaken the effect of the aids on health issues. Although validated questionnaires are used in this study, they remain mostly subjective, and may induce information bias.

Furthermore, adherence to treatments is a complex phenomenon which has been linked to 200 different covariates (43). In addition, social pressure and lack of resources/ self-confidence are known to worsen decisional conflict (25) but will not be assessed in this study. Asthma control is also a complex phenomenon for which every single predictor will not have been assessed. Thus, residual confounding effect is possible.

Recent knowledge translation theories suggest that the knowledge translation process is more multidirectional than linear (44). Since our knowledge translation model is linear, it could not be excluded that external factors, such as health literacy and numeracy skills, may play a role in the success or failure of our intervention.

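### The effect is taken from a GEE interaction whose protection against baseline-related loss that differs between arms depends on a working correlation the protocol does not name

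*Protocol*

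**What the plan says.** Protocol, Data analysis, fits generalised linear models with group, time and group-by-time effects, using a normal distribution and identity link for the continuous outcomes. It states: "The effect of the shared decision making aids on health outcomes will then be estimated by the interaction term between the group and time." For the two visits, "generalized estimating equations will be used in order to take repeated measures into account". The procedure named is PROC GENMOD. Table 6 in Annexe 1 repeats this model for decisional conflict and asthma knowledge, the two primary outcomes. No working correlation is given.

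Protocol, Bias, states: "Convenience sampling and loss to follow-up may induce selection bias in this pilot randomised controlled trial." Two steps follow: visit 2 is booked at the end of visit 1, and patients are telephoned in the week before it. Neither is an analysis step.

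Under Evaluation of the aids, the questionnaires are completed before the envelope is opened, so each randomised patient should have a baseline record even if visit 2 never takes place.

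**The concern.** The protocol names a threat and fixes an estimator whose resistance to that threat turns on a setting left open. A patient lost before visit 2 stays in the baseline mean and drops out of the 2-month mean. If, say, patients with high decisional conflict leave the aid arm more often than the control arm, the aid arm's mean falls although nobody has improved. Under an independence working correlation that fall enters the interaction as a treatment effect. The same algebra applies to asthma knowledge, and the bias can run in either direction.

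The covariate rule in Data analysis does not repair this. It deals with imbalance and confounding, and baseline decisional conflict is not in its list of covariates.

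**Working it through.** **Inputs from the protocol**
- Size: "50 patients are intended to be recruited to participate in the randomized control trial" (Sample size). Two arms; "Blocks of four will be used". I assume 1:1, so about 25 per arm.
- Test: a two-tailed p-value "less than 0.05 will be considered indicative of statistical significance".
- The only effect-size benchmark is for the Decisional Conflict Scale: "it is able to detect an effect size of 0.2 to 0.3 in studies that compare an intervention group to a control group".

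There is no planned figure to reproduce. The 50 rests on feasibility, and no SD, correlation, target effect or dropout rate is given ("Since the study is a pilot, power calculation will be made" afterwards).

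**Assumptions:** SD 15 points and equal at both visits; baseline to 2-month correlation ρ of 0.3 to 0.7; no true effect; loss as stated below.

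**Step 1. Algebra for one arm.** Let A be the baseline mean of all patients, B the baseline mean of completers and C the 2-month mean of completers. An independence GEE estimates the change as C − A. If loss depends only on baseline and there is no effect, C is on average A + ρ(B − A). With δ = B − A, the bias in that arm is ρδ. The bias in the interaction is ρ(δ_aid − δ_control).

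It follows that equal δ in both arms cancels, so baseline-related loss alone is not enough.

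**Step 2. An exchangeable structure.** The 2-month mean becomes C − α(B − A), where α is the estimated correlation. The remaining bias is (ρ − α)(δ_aid − δ_control), which is small because α is close to ρ.

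**Step 3. Large-sample check.** Simulation in SD units, ρ = 0.5 and 0.7, 10 to 30% loss. Where loss depends on baseline, the odds of loss change by a factor e per SD.

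| Pattern of loss | Independence, absolute bias | Exchangeable, absolute bias |
|---|---|---|
| Random in both arms | up to 0.004 | up to 0.003 |
| Same rate and same relation to baseline | up to 0.005 | up to 0.005 |
| Same relation, different rates (20 v 10, 20 v 5, 30 v 10%; ρ = 0.5 only) | 0.04 to 0.08 | up to 0.008 |
| Related to baseline in one arm only | 0.05 to 0.18 | up to 0.007 |
| Opposite directions in the two arms | 0.09 to 0.36 | up to 0.023 |

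A likelihood estimate was within 0.005 of zero wherever it was run (every row but the third).

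Check of Step 2: opposite directions, 20% loss, ρ = 0.7. The independence bias is 0.241 and α is 0.652. Predicted remainder: 0.241 × (0.7 − 0.652)/0.7 = 0.017. Simulated: 0.014.

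**Step 4. At the planned size.** 25 per arm, SD 15, ρ = 0.3 to 0.7, aid-arm loss related to baseline and control loss random:
- 5 v 5 lost: false benefit of 0.8 to 2.0 points. Divided by 15, this is 0.05 to 0.13 SD.
- 8 v 3 lost: 1.4 to 3.3 points, or 0.09 to 0.22 SD.
- Strong selection, 8 v 3 lost, ρ = 0.7, aid-arm completers 5.75 points below the whole arm at baseline: 0.7 × 5.75 = 4.0 points, or 4.0/15 = 0.27 SD.

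The likelihood estimate stays within about 0.1 point of zero in the first two cases.

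**Step 5. Against sampling error.** With complete follow-up the standard error of the interaction is √(2(1 − ρ)) × √(2/25). At ρ = 0.5 this is 1 × 0.283 = 0.283 SD. A bias of 0.1 to 0.2 SD is thus about 0.35 to 0.7 of a standard error.

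Simulated rejection rates at a nominal 5%, 25 per arm, ρ = 0.5 and 0.7, 10 to 30% loss:
- Independence, random loss: 5.4 to 6.5%.
- Independence, same mechanism in both arms: 5.8 to 7.1%.
- Independence, one arm selective: 6.4 to 9.6%.
- Independence, opposite directions: 6.4 to 22.4%, the top figure at 30% loss and ρ = 0.7.
- Exchangeable, all selective patterns: 5.8 to 7.6%.

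**The case against.** The strongest reply is that the fault lies in a setting the protocol does not fix. A working correlation and the handling of missed visits are commonly left to the SAP, which is not at hand, and their absence is not itself an error. This stands. It also limits the point: the bias belongs to one possible form of the stated estimator. What remains is that the protocol itself chose GEE and the procedure, and itself named the bias that this choice may not handle.

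Four stronger readings are tempting, and the documents do not support them.
- **GEE is the wrong method.** A reader might infer this, but with two visits and a normal, identity-link model an exchangeable GEE is nearly unbiased in every pattern examined.
- **Withdrawals alone create an effect.** They do not. The arms must differ in rate of loss or in its relation to baseline.
- **The protocol expects selection bias.** It says only that loss may induce it, and it plans two steps to limit loss.
- **The aid arm's extra task makes unequal loss likely.** That task is done once at visit 1, before a nurse meeting that both arms have, and visit 2 is the same in both. The protocol describes no extra burden during follow-up. Patients do open their own envelope and may know their group, so unequal loss cannot be excluded, but nothing shows it to be probable.

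It is also fair to say that most of the one-arm cases fall below 0.2 SD, the lower end of the only effect-size benchmark in the protocol.

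**Conclusion.** The point holds in a conditional form. If loss to follow-up differs between arms in rate or in its relation to baseline, the planned estimate depends on an unstated working correlation, and independence would bias it. With baseline-related loss in the aid arm only, the likely size is about 0.05 to 0.13 SD for 5 v 5 lost and 0.1 to 0.2 SD for 8 v 3 lost. It nears 0.3 SD only under strong selection, and exceeds that only when the arms select in opposite directions with 30% loss.

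SD, correlation, amount of loss and mechanism are all assumptions, because the protocol gives none. The calculations cover continuous outcomes only and say nothing about binary compliance. This is worth correcting because the remedy is cheap. It does not show that the trial's result will be biased.

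**What to change.** For the continuous outcomes, in Data analysis and Table 6, replace the GEE with a likelihood-based repeated-measures model with unstructured covariance. Include every randomised patient in the assigned arm with all available data. If PROC GENMOD is kept, specify an exchangeable working correlation and rule out independence. In either case, report loss by arm with the baseline decisional conflict and knowledge scores of those lost.

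Limiting the analysis to patients with both visits is no substitute: the bias per arm then becomes (ρ − 1)δ, which has the opposite sign.

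The cost is a change of procedure or one option, and about two sentences of text. No extra data or patients are needed, and the point estimate is unchanged if follow-up is complete. Neither option corrects loss that depends on unobserved 2-month values, and the protocol should say so.

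### GEE in PROC GENMOD with about 50 patients and no small-sample correction: if the uncorrected robust Wald method is used, the 95% intervals for the continuous outcomes are somewhat too short

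*Protocol*

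**What the plan says.** The Data analysis section models the continuous outcomes with a normal distribution and identity link, with terms for group, time and their interaction. These outcomes are asthma knowledge, decisional conflict, percent compliance and asthma control. The interaction is the effect of interest. For the two visits, "generalized estimating equations will be used in order to take repeated measures into account". The software is fixed: "SAS version 9.3 (SAS Institute Inc., Cary, USA) will be used to perform the statistical analyses, using PROC GENMOD". The threshold is fixed too: "A 2-tailed *p*-value less than 0.05 will be considered indicative of statistical significance". The footnotes to Table 6 add a 95% confidence interval for each effect and a p-value for the interaction term.

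The Sample size section states that "50 patients are intended to be recruited to participate in the randomized control trial", and adds: "If feasible, more than 50 patients may be enrolled in order to get sufficient statistical power". On allocation the protocol says "Blocks of four will be used", without giving the ratio. The Data analysis section also announces: "Exploratory subgroup analyses according to asthma severity will be conducted". The Inclusion criteria define three severity classes, and no class sizes are given.

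The protocol does not say whether the test is Wald or score, whether standard errors are robust or model-based, or whether a z or t reference applies. It mentions no small-sample correction.

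**The concern.** The usual robust GEE inference is a large-sample method. In a two-arm comparison of mean change it falls short in two ways when patients are few. The sandwich variance divides each arm's sum of squares by n where n − 1 would be unbiased. The ratio is then compared with 1.96, although a t quantile is needed because the variance is estimated. Both act in the same direction: the standard error is too small on average and the multiplier is too small.

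At stake are the intervals for both primary outcomes and the other continuous outcomes. For a pilot, the estimate and its interval are the main product, and they will guide any later trial. The effect is small with all patients included and grows quickly in subgroups of 5 to 10 per arm.

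**Working it through.** **Inputs.** From the protocol: two-sided 0.05; 50 patients; two arms; two time points; normal/identity model; effect = group-by-time interaction. Assumed: 1:1 allocation (25 per arm), normal data, equal variances, no dropout, and an uncorrected robust Wald statistic. Subgroup sizes are also assumed: 50 patients over three classes and two arms is 50/(3 × 2) ≈ 8 per arm, with 5 and 10 as a range. The protocol offers no power or error calculation to reproduce; the only stated figure is the 0.05 threshold.

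**Step 1: reduce the model.** With two visits and complete data, the interaction estimate equals the between-arm difference in mean change. Its uncorrected sandwich variance is SS₁/n₁² + SS₂/n₂², where SS is the sum of squared deviations of the changes within an arm. Fitting an exchangeable GEE to simulated data confirmed that estimate and standard error match this form, with or without baseline covariates as main effects.

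**Step 2: exact size.** With n per arm, the robust z equals the ordinary two-sample t statistic times √(n/(n − 1)). Rejecting when |z| > 1.960 is therefore the same as rejecting when |t| > 1.960 × √((n − 1)/n), on 2n − 2 degrees of freedom.

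- n = 25: 1.960 × √(24/25) = 1.920 on 48 df, error 0.0608
- n = 10: 1.960 × √(9/10) = 1.859 on 18 df, error 0.0794
- n = 8: 1.960 × √(7/8) = 1.833 on 14 df, error 0.0881
- n = 5: 1.960 × √(4/5) = 1.753 on 8 df, error 0.1177

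Coverage is one minus the error: 93.9%, 92.1%, 91.2% and 88.2%. At 20 per arm the error is 0.0637; at 40 per arm, 0.0566; at 4 per arm, 0.1405.

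**Step 3: simulation check.** Direct simulation of the statistic (200,000 trials per setting) gave 0.060 at 25 per arm, 0.088 at 8 and 0.116 at 5. Batches of 4,000 fitted GEEs at 25 per arm gave 5.7% and 6.5%, and 5.2% with five baseline covariates. The Monte Carlo standard error is about 0.4 points, so these batches scatter around the exact 6.1%. GEE fits gave 8.7% to 8.8% at 8 per arm and 11.2% to 12.0% at 5.

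**Step 4: alternatives.**

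- An n − 1 divisor with a t reference restores 5% under the same assumptions. The critical values are 2.011 (48 df), 2.145 (14 df) and 2.306 (8 df).
- A generalized score test in the same GEE framework gave 5.1% at 25 per arm, 5.4% at 8 and 5.5% at 5. This changes only the p-value; a Wald interval reported beside it keeps the coverage in step 2.

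**The case against.** The strongest objection is that the protocol never names the test being criticised. It says GEE and PROC GENMOD, and stops there. A score test is available within GEE and nearly removes the excess in the p-value. A reader might infer that the trial's actual error rate is 6%, and 9% to 12% in the subgroups. The documents do not support that: it depends on a choice left open and on subgroup sizes that appear nowhere. This part of the objection stands, and the point is conditional for that reason.

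It can also be said that variance estimators and reference distributions belong in an SAP, which may exist but is not at hand. This carries some weight. But the protocol itself commits to the estimation method, the procedure, the threshold and 95% intervals at this sample size. A score test would leave Wald intervals uncorrected, and the two could disagree about significance.

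Three further limits stand.

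- **Size.** The excess for the primary outcomes is about 1 percentage point, in a declared pilot, and it shrinks if more than 50 are enrolled.
- **Subgroups.** They are exploratory, so no confirmatory error rate is claimed for them. A reader might also infer a formal severity-by-treatment test. The protocol plans subgroup analyses for severity and speaks of statistical interaction only for body mass index, age, education and meeting length.
- **Binary compliance.** A reader might extend the argument to the log-binomial model. No inflation was shown there: simulation at 25 per arm, with assumed prevalences of 20% to 50%, gave 3.6% to 4.7%.

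**Conclusion.** The concern holds in conditional form, for the continuous outcomes only. If the uncorrected robust Wald test and interval are used, the two-sided error at nominal 0.05 is about 6% at 25 per arm, with coverage about 94%. In severity subgroups it is about 8%, 9% and 12% at 10, 8 and 5 per arm.

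These figures rest on normal data, equal variances, 1:1 allocation and no dropout, and the subgroup figures also on assumed sizes. The shortfall is minor for the primary outcomes and material only in small subgroups. It is worth correcting because its direction is predictable and the remedy needs no change of design.

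**What to change.** For the continuous outcomes and their severity subgroup analyses, name one small-sample method in the analysis text and take both p-values and confidence intervals from it. Either of these would do:

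- a repeated-measures linear model with unstructured covariance and Kenward-Roger degrees of freedom; or
- GEE with a bias-corrected sandwich variance and a t reference.

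The binary compliance model need not change on this account.

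The cost is a changed procedure or option and wider intervals. Under the assumptions above, the ratio of multipliers is 2.011/1.920 = 1.047 at 25 per arm, so about 5% wider. It is 2.145/1.833 = 1.17 at 8 per arm and 2.306/1.753 = 1.32 at 5. The larger widening in small subgroups reflects how little information they hold. No extra data or patients are needed.

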| Years with asthma          | X                                              | X                             | Mean (standard deviation) |

Table 5: Comparative analysis of dependent variables at baseline

| Covariate                  | Intervention group
(shared decision making) | Control group
(usual care) | Test                       | P-value |
|----------------------------|------------------------------------------------|-------------------------------|----------------------------|---------|
| Primary outcomes    |                                                |                               |                            |         |
| Decisional conflict        | X                                              | X                             | Student t -test     | X       |
| Asthma knowledge           | X                                              | X                             | Student t -test     | X       |
| Secondary outcomes  |                                                |                               |                            |         |
| Compliance with treatments | X                                              | X                             | Pearson's chi-squared test | X       |
| Compliance with:           |                                                |                               |                            |         |
| Controller medication      | X                                              | X                             | Student t -test     | X       |
| Rescue medication          | X                                              | X                             | Student t -test     | X       |
| Add-on therapy             | X                                              | X                             | Student t -test     | X       |
| Asthma control             | X                                              | X                             | Student t -test     | X       |

Table 6: Effect\* of shared decision making aids on dependent variables

| Dependent variable         | Baseline |    | 2 month |    | Model                    | Distribution | Link     | Group
IG CG | Time
T1 T2 | Interaction term
$G \times T$ | Significance |
|----------------------------|----------|----|---------|----|--------------------------|--------------|----------|----------------|---------------|----------------------------------|--------------|

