**IG:** Intervention group (shared decision making) **CG:** Control group (usual care) **T1:** Baseline **T2:** 2-month follow-up

\* The effect of shared decision making aids on health outcomes will be estimated with their 95% confidence interval. The effect of the aids on asthma knowledge, decisional conflict, compliance with

controller/rescue/add-on pharmacotherapy, and asthma control will be expressed as means, since these variables are continuous. On the other hand, the effect of the aids on compliance with treatments (a binary variable) will be expressed as prevalence ratios. Both types of model will adjust for covariates, if a confounding variable results in a  $\geq 10\%$  change of the effect measure.

† P-value of the interaction term.

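### Covariates are chosen from the data, yet for the continuous outcomes with both visits observed, baseline covariates cannot move the group-by-time effect, so the 10% rule does nothing there; where it can act, it acts for poor reasons

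*Protocol*

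**What the plan says.** The protocol's Data analysis section has two rules for choosing covariates, both applied after the data are in.

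- **Imbalance.** If any of six listed covariates (asthma knowledge, age, body mass index, atopy, environmental triggers, respiratory tract infections) "are not distributed evenly between groups, we will adjust for them in analyses". No criterion for uneven is given.
- **Change in estimate.** "Predictors of health outcomes will be incorporated into the model as confounders if they result in a >10% change in the effect measure", by a backward procedure. The footnote to Table 6 in Annexe 1 repeats only this rule: "Both types of model will adjust for covariates, if a confounding variable results in a" change of at least 10%. The strict and non-strict thresholds differ slightly, which is minor.

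The same section fixes the effect measure to which the second rule refers. In the models, "effects for group (intervention and control), time (baseline and 2-month follow-up) and group-by-time interaction will be included", and "The effect of the shared decision making aids on health outcomes will then be estimated by the interaction term between the group and time". For knowledge, decisional conflict, percent compliance and asthma control, "a normal distribution and an identity link will be used, since all 4 variables are expressed as continuous ones". For the all-criteria compliance variable, "a binomial distribution and a log link will be used as this variable is expressed as a binary one". Generalised estimating equations (GEE) handle the repeated measures.

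The section on predictors of asthma control, and Table 2, place covariate measurement at baseline. The one exception is respiratory infection in the last month, which is asked again at 2 months.

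**The concern.** The rules and the effect measure do not fit together. A change-in-estimate rule presupposes that adding the covariate can change the estimate. Here the estimate is a between-arm difference in within-patient change, and all but one of the candidates have a single value per patient. For both primary outcomes the planned adjustment may therefore do nothing: the rule would never select a covariate, and a covariate added for imbalance would alter neither the estimate nor its precision.

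Where the rule can select something, the covariate set is no longer fixed in advance. It would follow the outcome data, a value recorded after randomisation, or the pattern of missing second visits. At stake are precision that a trial of 50 patients could otherwise gain, and an adjustment set that a reader can verify was not chosen from the results.

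**Working it through.** The protocol gives no figure on this point: the 50 patients are a pilot number, and power is left to be computed afterwards. The check is therefore algebra first, then illustrations with assumed inputs.

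**1. Continuous outcomes, both visits observed.** Let G be group, t = 0 or 1 the visit, and X a covariate measured only at baseline:

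Y(i,t) = β0 + β1·G(i) + β2·t + β3·G(i)·t + γ·X(i) + e(i,t)

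The within-patient change is

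D(i) = Y(i,1) − Y(i,0) = β2 + β3·G(i) + [e(i,1) − e(i,0)].

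The term γ·X(i) has cancelled. Under a common variance, a patient's mean and change are uncorrelated in the working model, and X enters only the equation for the mean. With complete pairs the estimate is therefore

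b3 = mean of D in the intervention arm − mean of D in the control arm,

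with or without X. The robust standard error uses the residuals of D about the arm means, which do not contain X either. The working correlation is not stated, but with two visits it has only one off-diagonal value, and the result does not depend on it.

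Numerical confirmation (generated data, N = 50, age and knowledge imbalanced): the interaction was −5.9028 with standard error 3.5968, both without covariates and with age and knowledge, under independence and under exchangeable correlation. Over repeated data sets the largest change was 1.4 × 10⁻¹⁴ (rounding error), the ratio of standard errors was 1.0000, and 0% of trials met the 10% rule.

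**2. Where the estimate can move.** Simulated with N = 50 at 1:1. Covariate effects, standard deviations, treatment effect and dropout rates are assumptions, because the protocol gives none.

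| Situation | Median change in effect | Share of trials above 10% |
|---|---|---|
| Binary compliance, log link, complete data, one baseline covariate (377 converged fits) | about 6% | about 29% |
| Infections entered as a two-visit variable, continuous outcome, complete data | about 12% | about 54% |
| Visit 2 missing at random in 5%, 10%, 20%; exchangeable correlation | 1.8%, 3.3%, 6.1% | 4% to 35% |
| The same; independence correlation | 4.7%, 5.8%, 11.3% | 28% to 53% |

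The continuous scenarios used 80 to 100 data sets each. A share of 54% from 100 data sets has a Monte Carlo standard error of √(0.54 × 0.46/100) ≈ 0.05, so these are orders of magnitude. In the dropout rows the movement comes from who is missing and from the unstated working correlation, not from confounding.

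**3. What a prespecified baseline-adjusted model gains.** With equal variance σ² at the two visits and correlation ρ:

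- variance of the change per patient: 2σ²(1 − ρ)
- residual variance of the 2-month value given baseline: σ²(1 − ρ²)
- ratio: (1 − ρ²)/[2(1 − ρ)] = (1 + ρ)/2

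For assumed ρ of 0.3, 0.5 and 0.7 the ratio is 0.65, 0.75 and 0.85. The corresponding standard error ratios are √0.65 ≈ 0.81, √0.75 ≈ 0.87 and √0.85 ≈ 0.92. This ignores the small cost of estimating the baseline slope.

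**The case against.** The planned interaction contrast is valid. Taking each patient's change already removes any additive, time-constant effect of a covariate, and that is why the covariate drops out. It is therefore not fair to say that imbalance is left wholly uncorrected. This stands. What is lost is precision, together with any handling of covariate-related change or regression to the mean.

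The protocol also does not say in what form covariates enter. A statistical analysis plan could add covariate-by-time terms, and these would move the interaction. That too stands as a limit on the algebra. However, the only covariate interactions that the protocol names are exploratory ones for effect modification, not adjustment.

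A reader might infer that the whole adjustment plan is empty and can never change any effect. The documents do not support that: binary compliance uses a log link, infections are recorded twice, and the Bias section expects some loss to follow-up.

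A reader might also infer that the rule routinely picks up noise covariates, so that the p-values lose their meaning. That would need a model of the 2-month value alone, which the protocol does not plan. Table 2 also maps six candidates only to asthma control, two to compliance, one to decisional conflict and none to knowledge as an outcome. Even in that unplanned model, a null simulation with N = 50 and assumed covariate effects of 0 or 0.3 SD gave a two-sided type I error of 4.5% to 5.1% with one candidate and 3.5% to 5.8% with six. How often covariates are selected is not the same as error inflation.

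The baseline tests in Annexe 1, Table 5 ("Comparative analysis of dependent variables at baseline") are a side issue. They concern outcomes, Table 3 on covariates has no test column, and neither selection rule uses the p-values.

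**Conclusion.** The point holds in a limited form. For knowledge, decisional conflict, percent compliance and asthma control, with both visits observed and baseline-only covariates entered as main effects, adjustment changes neither the interaction nor its robust standard error. The 10% rule cannot be met there. This is exact and rests on no assumed effect size, SD or correlation.

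Elsewhere the rule can act, and it then chooses covariates from outcome data, from a post-randomisation infection record or from the pattern of missing visits. How often it would do so depends on assumed inputs; the shares in the table are illustrations only.

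The planned analysis is not invalid, and no inflation of the error rate has been shown. The cost is an adjustment plan that is inert for both primary outcomes in complete data and not fixed in advance elsewhere. It also forgoes a variance reduction of about 15% to 35% (1 − 0.85 to 1 − 0.65) for assumed correlations of 0.7 down to 0.3.

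**What to change.** - Delete both selection rules from Data analysis and the matching sentence in the Table 6 footnote. This also removes the mismatch between the two 10% thresholds.
- Name now, for each outcome, a small set of baseline covariates from those mapped in Table 2, and include them whatever the observed balance. For example, use baseline knowledge for decisional conflict and compliance, and age for asthma control. Table 2 maps none to knowledge as an outcome, so its own baseline score is enough. Do not adjust for infections recorded at 2 months.
- For the continuous outcomes, estimate the effect from the 2-month value adjusted for its baseline value. In that model the named covariates can do some work.
- Optionally, drop the tests and p-values from Table 5.

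The cost is a real change to the primary model stated in Data analysis and Table 6, so it should be made as a documented amendment before outcome data are compared by group. All the baseline values are already to be collected, so no new data or visits are needed.
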